### Relationship to study intervention

The principal investigator (PI) will assess all AEs and SAEs to determine whether there is any potential relationship to the study intervention. The relationship will be assessed as either “related” or “unrelated” as below:*Related*: There is a reasonable possibility that the study intervention caused the AE or SAE, or there appears to be a temporal relationship between the administration of the study intervention and the event.*Unrelated*: There does not seem to be a reasonable possibility that the administration of the study intervention caused the AE or SAE, there does not appear to be a temporal relationship between the study intervention and event onset, or there has been an alternate etiology established that explains the event.

### AE and SAE reporting

All AEs and SAEs will be captured on the *adverse events log*.

The PI will be responsible for notifying the approving HREC of any SAE, independent of the relatedness to the study, within 7 calendar days upon initial receipt of the information. If the SAE is considered as related to the IP, a report must follow within 7 days of learning about the SAE.

### Period for collecting AEs/SAEs

The period for collecting AEs and SAEs (“active collection period”) for each participant is as follows:AEs: From informed consent until the end of study involvement (week 20).SAEs: From informed consent until study completion.

### Participant withdrawal and/or discontinuation from the study

Participants will be informed they may withdraw from the study at any time. This will be explained during the consent process and is detailed in the ICF. Participants will be made aware they may be discontinued at any time at the discretion of the investigators for safety reasons, or the inability of the participant to comply with the protocol-required schedule of study visits or procedures. Investigators may discontinue or withdraw a participant from the study for the following reasons:Non-compliance to study protocol.Occurrence of AE related to the intervention, laboratory abnormality, or other medical condition such that participation in the study would not be in the best interest of the participant. This includes whether the participant meets an exclusion criterion (newly developed or not previously recognized).Disease progression requiring discontinuation of the study intervention.

Throughout the duration of the study, the research team will evaluate the well-being of all participants. If continued participation is considered harmful to an individual’s health or safety, that participant will be withdrawn from the study. If a participant is discontinued or withdraws from the study, every attempt will be made to have them complete an Early Termination Visit to determine the participant outcome, to ensure they are withdrawn safely, and to close off any unresolved AEs, if possible. Participants who withdraw after randomization will not be replaced.

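### The withdrawal rule does not separate stopping the product from leaving the study, so week-16 outcomes can be lost for reasons plausibly tied to tolerability and function

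*Protocol article*

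**What the plan says.** The section on participant withdrawal and discontinuation treats the two as one event. Its lead-in is "Investigators may discontinue or withdraw a participant from the study for the following reasons", and three grounds follow:

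- "Non-compliance to study protocol".
- A related AE, a laboratory abnormality, or "other medical condition such that participation in the study would not be in the best interest of the participant". The text adds: "This includes whether the participant meets an exclusion criterion (newly developed or not previously recognized".
- "Disease progression requiring discontinuation of the study intervention".

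These grounds are discretionary. One rule is mandatory: "If continued participation is considered harmful to an individual’s health or safety, that participant will be withdrawn from the study".

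For anyone who leaves, "every attempt will be made to have them complete an Early Termination Visit to determine the participant outcome", and also to withdraw them safely and close open AEs. Those who withdraw after randomization are not replaced.

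Three other sections bear on this. The Abstract and Study assessments place the primary outcomes at baseline to week 16, with tests at baseline and weeks 8, 16 and 20. Statistical analyses and power limits the primary intention-to-treat (ITT) analysis to participants who complete the trial, and adds a secondary analysis of those who took at least 90% of the supplement. Period for collecting AEs/SAEs sets the AE window as "From informed consent until the end of study involvement (week 20".

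**The concern.** Stopping a product and ceasing to be observed are different events. An intention-to-treat comparison needs week-16 outcomes from participants who stopped, adhered poorly or became unwell. Here the same discretionary list covers both events, and the third ground makes the need to stop the product a reason to leave the study.

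The grounds are not neutral with respect to outcome. Among the exclusion criteria that could be newly met are a disorder that prevents function testing, a recent limb fracture, and unintentional weight loss. Some of these are close to the functional decline that the trial measures. If such participants leave, and leave differently in the two arms, the remaining week-16 comparison can be biased. AEs arising after an early exit may also go unrecorded. This is a fault of data collection, so it remains even if the analysis set is renamed or redefined.

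**Working it through.** **Passages side by side**

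1. *After an exit.* The withdrawal section offers one attempted visit. It does not say whether the Short Physical Performance Battery (SPPB), handgrip or timed up-and-go (TUG) is measured there, and it gives the visit no fixed week. No other section keeps a participant who has stopped the product on the week-8, 16 and 20 schedule.
2. *Inability to perform.* Table 1 gives 0 points for being unable to do the gait or chair-rise test. On the SPPB such a participant can still be scored, and removal discards that score.
3. *Non-compliance.* A separate analysis at 90% adherence or more has a purpose only if less adherent participants stay in the main set. Removal for non-compliance works against that. The article does not define non-compliance, so how far the two sets would converge is unknown.
4. *AE window.* The end of involvement is equated with week 20. For a participant withdrawn at week 9, say, these are two different dates, and the text does not say which governs.
5. *Analysis set.* A longitudinal model could use the week-8 data of those who leave, but the primary analysis is limited to completers.

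**How many could be affected**

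Inputs from Statistical analyses and power: 74 participants, 37 per group, dropout about 30%.

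- Expected dropout: 0.30 × 74 = 22.2, about 22 participants.
- Remaining per group: 37 × 0.70 = 25.9, about 26.

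The 30% is an allowance for dropout from all causes. It is an upper bound on the share affected by this rule, since consent withdrawal and loss to follow-up also fall within it.

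**Power is not the main risk.** On the protocol's own d = 1.2, the two-sided power at 26 per group without a covariate is Φ(1.2 × √(26/2) − 1.96) = Φ(2.37), about 99%. The question is bias.

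**Illustration of bias.** The inputs below, other than r = 0.7, are assumptions and are not in the documents. Let p be the share removed in an arm, and δ the amount, in SD, by which those removed would have scored worse at week 16 than those who stayed, after allowing for baseline. Within an arm, the mean of all randomized = completer mean − pδ. Hence, for an outcome where higher is better,

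bias in the difference = p_S·δ_S − p_P·δ_P (S synbiotic, P placebo).

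- Equal and uninformative removal: bias = 0.
- Removal differing by 10 percentage points, same δ in both arms: 0.10 × 0.5 = 0.05 SD, or 0.10 × 1.0 = 0.10 SD.

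Standard error with 26 per arm and baseline adjustment at r = 0.7: √(2/26) × √(1 − 0.49) = 0.277 × 0.714 = 0.198 SD.

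Rejection rate with no true effect = P(|Z + bias/SE| > 1.96):

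| Residual bias (SD) | bias/SE | Rejection rate |
|---|---|---|
| 0 | 0 | 5.0% |
| 0.05 | 0.25 | 5.7% |
| 0.10 | 0.50 | 8.0% |

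The bias must be what remains after baseline adjustment. If 0.05 and 0.10 SD were unadjusted shifts and removal followed the week-16 score, about 1 − 0.7² = 51% would remain: 0.026 and 0.051 SD, with rejection rates of about 5.2% and 5.7%.

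**The case against.** The best defence has four parts.

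- *The grounds are permissive.* Investigators may withdraw someone; withdrawal is required only where continuing is considered harmful. The AE and exclusion-criterion ground is tied to the participant's best interest, and stopping the product for any reason is not a listed ground. This stands. A reader might infer that week-16 and week-20 outcomes are never collected once the product is stopped. The text does not support that: data are lost only for those actually removed before the visit.
- *The Early Termination Visit is there to determine the participant's outcome.* This also stands, and some function data may come from it. But it is not a week-16 assessment.
- *An article leaves detail to the full protocol (v1.2), which is not shown.* This is fair for the list of tests at the Early Termination Visit, and its absence alone would be no finding. The point rests on a rule that the article does state: removal is from the study, on grounds that include having to stop the product.
- *The AE window is stated per participant to week 20, and to study completion for serious events.* A reader might infer that AEs after early stopping go uncounted. That is possible but not stated; the wording is ambiguous.

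Discretion does not remove the problem. It makes the missing data depend on investigators' judgement, although blinding of site staff limits deliberate differences between the arms.

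**Conclusion.** The point holds in limited form. The withdrawal section does not separate stopping the product from leaving the study. At the investigator's discretion, several events plausibly related to tolerability or function can end participation, with only an Early Termination Visit attempted afterwards. Week-16 outcomes, and possibly AEs to week 20, can be lost this way. The rule also sits badly with the separate adherence analysis, and the completer restriction on the primary analysis compounds it.

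Neither the size nor the direction of any bias can be derived from the documents. The range of 5.7% to 8.0% is an illustration that rests on an assumed residual bias of 0.05 to 0.10 SD, 26 per arm and r = 0.7. Larger figures follow only from stronger assumptions about imbalance, or from attributing all of the roughly 30% dropout to this rule, and the documents support neither.

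**What to change.** Amend the withdrawal section as follows:

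- Define discontinuation of the product and withdrawal from the study as separate events, and record each with its date and reason.
- State that participants who stop the product, are non-compliant, or are found to meet an exclusion criterion are invited to the scheduled week-8, 16 and 20 function tests and AE review, provided that they consent and the investigator does not judge continued participation harmful. Where they cannot attend, keep AE contact to week 20.
- For those who decline further visits, include SPPB, handgrip and TUG at the Early Termination Visit and record its actual week.
- Reconcile this section with the completer-based ITT set and the adherence analysis in Statistical analyses and power, and with the AE window in Period for collecting AEs/SAEs.

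When the product is stopped, and the existing withdrawal where participation is considered harmful, stay as written.

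The cost is a short amendment with ethics approval and a registry update, plus effort to retain participants. The visits themselves are already on the schedule. Some off-treatment visits will slightly dilute the observed effect. Enrolment was expected to finish in April 2024, so the change helps only participants still in follow-up when it takes effect.

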### Ancillary and post-trial care

The study team will ensure proper and safe conduct of the trial and will strive to mitigate risks to participants associated with their involvement. Due to the wide safety profile of the investigational product, we do not anticipate the need for compensation due to harm, and there are no provisions for ancillary or post-trial care. Likewise, we do not expect there to be cause for terminating the trial. However, in the event a participant is harmed as a direct consequence of their involvement, they will be referred to their treating health practitioner and directed to contact the Swinburne University Human Research Ethics Committee. This information is included in the consent forms and will be discussed at the screening appointment. There are no provisions for post-trial access to the intervention.

### Compliance with study intervention

Participants will be instructed to take their allocated study intervention once daily for 16 weeks. At week 8 (mid-intervention) and week 16 (end-of-intervention), participants will be asked to return their study IP (including unused supplements and empty packaging). IP accountability will be performed to confirm compliance with the required dosing schedule. In addition, participants will be asked to complete and return a study supplement adherence log, which will be reviewed in week 8 and 16 visits.

### Recruitment and retention

Local, community-dwelling individuals will be invited to participate. Recruitment will occur via various mailing lists, hard-copy flyers, and social media outlets. It is anticipated the majority of enrolment may be from participants of previous studies who have consented to future contact. See Supplementary File 2 for the Recruitment Plan. Once enrolled, retention strategies will include systematically scheduling future appointments, SMS appointment reminders and verbally confirming upcoming appointments at each visit.

### Data collection and management

#### Confidentiality of data

To maintain privacy, participants will be randomly assigned unique study identification numbers. Data collection forms (DCFs) will be developed before the onset of the trial. DCFs for each participant will be completed by a study investigator. All essential data (DCFs, source documents, signed consent documents and study logs) will be securely stored in a locked cabinet in the research site office accessible only to the PI and delegated research staff. De-identified study data will be collected and managed using research electronic data capture (REDCap) tools [82]. The PI and delegated research staff will have access to the final datasets.

#### Data collection

Investigators will be trained and delegated by the PI for all study requirements, including specimen collection, eliciting of information from participants in a uniform and reproducible manner, and the standardized approach to all study assessments described above. DXA scans will be conducted by trained, blinded staff who hold current certifications.

#### Data monitoring

The blinded research team will conduct ongoing monitoring of the study to confirm the safety and rights of all participants are protected, that the currently approved study protocol is being followed and to verify data collected is complete and accurate. This trial will be conducted in accordance with the ethical principles for medical research involving human subjects described in the Declaration of Helsinki [83] and consistent with the International Conference on Harmonisation Good Clinical Practice (ICH-GCP) and applicable regulations of Australia. The research team will perform internal quality control (QC) procedures to confirm source data and biological specimen collection and documentation are completed as per study protocol. Data QC checks will also be regularly generated within the REDCap database to ensure data entry is accurate and complete. This will be a small (*n* = 74), single-site RCT, and the blinded study team will manage and monitor trial data; as such no formal data monitoring committee (DMC) will be formed. Any protocol deviations (PDs) or violations (PVs) will be documented in the study records and reported in accordance with HREC requirements.

## Discussion

In this manuscript, we present a protocol to examine the effects of a synbiotic on physical performance in an older population. Gut dysbiosis has been associated with increasing biological age [84]. Evidence from animal and human studies supports the role of the gut microbiome in maintaining lean body mass and physical functioning [16].

A high percentage of healthcare costs in elderly populations arise from the negative outcomes resulting from reduced skeletal muscle mass and strength [85]. Sarcopenia has been shown to represent a significant but modifiable economic burden on healthcare services worldwide [86]. Goates et al. estimated the total cost of hospitalizations for individuals with sarcopenia was USD 40.4 billion in the USA alone [87]. Older adults are the fastest-growing global subpopulation and by 2025 the number of people with sarcopenia is predicted to increase to 1.2 billion [88]. Therefore, a better understanding of mechanisms that underlie the maintenance of skeletal muscle mass, strength, and physical performance may provide valuable insight to help address the public health priority of healthy aging. The gut microbiome may be involved in the maintenance of these outcomes. Existing evidence has focused on the diversity of the gut microbiota rather than the functional capacity of its microbiome. Studies exploring the evolving role of gut microbial changes resulting in the loss of skeletal muscle or with specific measures of physical function remain inconclusive. To our knowledge, no human studies have yet investigated utilizing synbiotic (pre- and probiotic combination) interventions to influence gut microbiota and the association with measures of physical performance in elderly, community-dwelling individuals.

Therefore, the current RCT aims to provide a greater understanding of the relationship between gut microbiota, its microbiome and measures of physical function and muscle health in older adults that may ultimately help in reducing the progression of sarcopenia and/or frailty. If proven effective, the outcomes of this project may provide further evidence to support the development of targeted interventions (i.e., synbiotics) to influence the microbiota composition leading to the maintenance of skeletal muscle mass and strength and improved physical performance in elderly populations.

Given the growing interest in the role of microbial populations in the aging gut, further research is needed to confirm and/or extend some of these initial findings. An improved understanding of the impact of the gut microbiome on skeletal muscle could have a dramatic effect on improving the health and quality of life for the elderly, reducing associated comorbidity and disability, and stabilizing rising healthcare costs. It is anticipated that the outcomes of this project may describe the safety and tolerability of therapeutic microbiome manipulations and further explore the utility of targeted interventions to maintain muscle mass and improve physical functioning in elderly populations.

### Trial status

This trial will be conducted according to the current ethics-approved Protocol (v1.2, 25 Jun 2022). Protocol amendments, defined as any modification to the study objectives, design, or procedures that impact participant safety or conduct of the study, will be approved by SUHREC before implementation in the trial. Any such protocol amendments will be communicated to all investigative site staff and will be updated on ANZCTR. These modifications will be communicated to participants at their next scheduled appointment and, if appropriate, will be reflected in revised SUHREC-approved ICF documents that will be discussed with all participants before obtaining re-consent. Supplementary File 3 provides the protocol amendment history. Recruitment for this study commenced in November 2022 and the enrolment target is expected to be met in April 2024.

### Universal trial number

U1111-1277–2798

## Data Availability

The datasets generated from this trial will be available from the corresponding author upon reasonable request.

## Abbreviations

AE: Adverse event
ALM: Appendicular lean mass
ANZCTR: Australian New Zealand Clinical Trials Registry
ASMM: Appendicular skeletal muscle mass
BIA: Bioelectric impedance analysis
BMI: Body mass index
CBC: Complete blood count
CC: Calf circumference
CFU: Colony-forming unit
CMP: Comprehensive metabolic panel
CSA: Cross-sectional area
DCF: Data collection form
DUHREC: Deakin University Human Research Ethics Committee
DXA: Dual-energy X-ray absorptiometry
EDTA: Ethylene diamine tetraacetic acid
EI: Echo intensity
EWGSOP: European Working Group on Sarcopenia in Older People
FFM: Fat-free mass
FL: Fascicle length
GCP: Good Clinical Practice
GIT: Gastrointestinal tract
HREC: Human Research Ethics Committee
ICF: Information and Consent Form
ICH-GCP: International Conference on Harmonisation- Good Clinical Practice
ICMJE: International Committee of Medical Journal Editors
IP: Investigational product
ITT: Intention to treat
LBM: Lean body mass
LSTM: Lean soft tissue mass
MNA-SF: Mini Nutritional Assessment- Short Form
MT: Muscle thickness
NIH: National Institutes of Health
PA: Pennation angle
PI: Principal investigator
QC: Quality control
RCT: Randomized controlled trial
RF: *Rectus femoris*
rRNA: ribosomal RNA
SAE: Serious adverse event
SARCUS: SARCopenia through UltraSound
SCFA: Short-chain fatty acid
SMI: Skeletal mass index
SPIRIT: Standard Protocol Items Recommendations for Interventional Trials
SPPB: Short Physical Performance Battery
SST: Serum separator tube
SUHREC: Swinburne University Human Research Ethics Committee
TUG: Timed up-and-go
USI: Ultrasound sarcopenia index
VI: *Vastus intermedius*
WGS: Whole-genome sequencing
